**Methods:**

A quasi-experimental design with repeated observations, taken at baseline, post-intervention, and at one and three months post-intervention, in people hospitalized with cognitive disorders or dementia. The study will be carried out in four general hospitals in Spain and will include 430 PwD and their caregivers. The intervention was previously developed using the Balance of Care methodology where nurses, physicians, social workers and informal caregivers identified the best practices for this specific care situation. We aim to personalize the intervention, as recommended in the literature. The study has an innovative approach that includes new technologies and previous scientific evidence. Valid, reliable instruments will be used to measure the intervention outcomes. Quality of care and comorbidity will be analyzed based on the use of restraints and psychotropic medication, pain control, falls, functional capacity and days of hospitalization. Continuity of care will be measured based on post-discharge emergency hospital visits, visits to specialists, cost, and inter-sectorial communication among healthcare professionals and informal caregivers. Statistical analysis will be performed to analyze the effect of the intervention on quality of care, comorbidity and continuity of care for patients with dementia.

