### Setting and participants

The study will be conducted in four traumatology units at high technology public hospitals across Spain. The autonomous communities included are Catalonia (Hospital Clinic Barcelona), Madrid (Hospital Puerta de Hierro Majadahonda), Cantabria (Hospital Universitario Marqués de Valdecilla) and Navarra (Complejo Hospitalario de Navarra). The study will be held in a 3-year frame time, with control group data collection starting in in August 2018.

Participants will be PwD and their caregivers (*n* = 432), and healthcare professionals working in the traumatology unit (*n* = 85). Patients will be recruited consecutively in two groups from emergency department admissions for surgery (See Table 1):
Control group: People with dementia or cognitive impairment hospitalized with proximal femur fracture under surgery and their informal caregivers receiving usual nursing care. The main aspects covered in usual nursing care include control of pain, mobility, drainage and wound assessment, mobilization and nutrition following the established guidelines for each hospital.Experimental group: People with dementia or cognitive impairment hospitalized with proximal femur fracture under surgery and their informal caregivers receiving the intervention (CARExDEM).All healthcare professionals working in traumatology units (nurses, care assistants, physiotherapists, social workers and physicians) will answer an ad hoc questionnaire to assess knowledge in care of PwD before and after the intervention.

**Table 1 Tab1:** Data collection summary. (*HCB* Hospital Clinic Barcelona, *HPHM* Hospital Puerta Hierro Majadahonda, *HMV* Hospital Universitario Marqués de Valdecilla; *CHN* Complejo Hospitalario de Navarra)

	Data collection 1	Data collection 2	Data collection 3	Data collection 4
**Control Group** People with dementia or cognitive impairment admitted to traumatology units receiving usual care	HCB (*n* = 54)	HCB (*n* = 54)	HCB (*n* = 54)	HCB (*n* = 54)
	HPHM (*n* = 54)	HPHM (*n* = 54)	HPHM (*n* = 54)	HPHM (*n* = 54)
	HMV (*n* = 54)	HMV (*n* = 54)	HMV (*n* = 54)	HMV (*n* = 54)
	CHN (*n* = 54)	CHN (*n* = 54)	CHN (*n* = 54)	CHN (*n* = 54)
INTERVENTION: CARExDEM Program				
**Experimental Group** People with dementia or cognitive impairment admitted to traumatology units receiving the intervention	HCB (*n* = 54)	HCB (*n* = 54)	HCB (*n* = 54)	HCB (*n* = 54)
	HPHM (*n* = 54)	HPHM (*n* = 54)	HPHM (*n* = 54)	HPHM (*n* = 54)

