### Follow-up and assessment of the CARExDEM implementation

After implementation, data will be collected for the experimental group using the same instruments and organization as those for the control group. Weekly meetings will be held for follow-up and to provide support to the interviewers and ward staff. A data manager will input data into a database and results will be evaluated by an expert statistician. Results will be disseminated through journals and congresses.

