## Statistical analysis

Descriptive analysis will be used for baseline data. Categorical variables will be represented with absolute frequencies and percentages. For continuous variables, mean values, standard deviation or medians will be calculated. To study the effect of the intervention, analysis of co-variance will be carried out (ANCOVA), with Student’s t-test for continuous variables and McNemar’s test for categorical variables. Sensitivity will be analyzed to compare basal data of participants who complete the study with those who do not. Main outcome measures include quality of care and comorbidity (physical restraints, psychotropic medication, falls, functional capacity, pain assessment, length of hospital stay and number of readmissions); continuity of care (informal caregiver reaction, multidisciplinary and intersectoral communication) economic costs of hospital and community care and nurses’ level of knowledge in acute care of PwD. Outcomes measured will assess longitudinal changes from all the collection phases; baseline (admission), discharge, 1 month and 3-month follow-up, comparing pre-intervention and post-intervention values. Confidence intervals of 95% will be calculated. Values of *p* < 0.05 will be considered significant. Statistical analysis will be performed with R-3.2.3. for Windows. The research team will reflect on the analyzed data and issue a final report including the CARExDEM program with the required modifications identified following the implementation evaluation. This will ease the subsequent implementation of the program in other hospitals.

For the sample calculation, we estimated that a sample of 432 participants need to be included in the study, assuming an improvement in patients with pain around 50%, with precision of 5%, a confidence interval of 95 and 10% of dropouts. Only the research team and data manager will have access to data.

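### McNemar's test is the only test named for the intervention effect on categorical outcomes, but the control and experimental groups are different, unmatched patients

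*Protocol article*

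**What the plan says.** The Statistical analysis section begins its methods sentence with "To study the effect of the intervention, analysis of co-variance will be carried out (ANCOVA" and continues, after the bracket, "with Student’s t-test for continuous variables and McNemar’s test for categorical variables". No other test for categorical variables is named. The main outcomes listed there for quality of care and comorbidity are "physical restraints, psychotropic medication, falls, functional capacity, pain assessment, length of hospital stay and number of readmissions". The section adds that change will be followed across the four collection points, "comparing pre-intervention and post-intervention values".

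The design is set out under Setting and participants: "Patients will be recruited consecutively in two groups from emergency department admissions for surgery". The control group consists of patients and "their informal caregivers receiving usual nursing care"; the experimental group receives CARExDEM. Table 1 gives 54 patients at each of four hospitals in each group. The section on follow-up and assessment of the implementation fixes the order: "After implementation, data will be collected for the experimental group using the same instruments and organization as those for the control group". The article nowhere matches a control patient to an experimental patient.

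**The concern.** McNemar's test compares two binary readings on the same person or on a matched pair. It uses only the discordant pairs, those positive on one reading and negative on the other. With two separately recruited groups, there are no pairs across the contrast that carries the intervention effect.

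The only pairing available among patients is between visits of the same patient. An analyst who follows the sentence literally could run the test from admission to discharge in the experimental group and report the result as the effect of CARExDEM. That result would mix the programme with whatever happens to any patient after an operated femur fracture. The categorical main outcomes would then have no valid between-group test, in a non-randomised comparison of successive cohorts where that contrast most needs care.

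**Working it through.** **Inputs from the article.** Two groups of 4 × 54 = 216 patients; 10% dropout, so 216 × 0.9 = 194 evaluable per group; significance at p < 0.05, taken as two-sided. The background figure of 25% for restraint use is borrowed only as an illustrative control rate. Every other rate and correlation below is an assumption.

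**1. Does the stated sample size depend on McNemar's test?** With the article's 50%, 5% precision and 95% confidence, n = z²p(1−p)/d² = 1.96² × 0.25 / 0.05² = 384.2. Dividing by 0.9 for dropout gives 427 (428 if 385 is used). This is close to the stated 432, which equals 8 × 54. It is a one-proportion precision formula, with no paired test and no two-group test in it, so changing the test does not undo the stated figure.

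**2. McNemar's test across the groups.** The statistic is (b−c)²/(b+c), where b and c are the discordant pair counts. Suppose 54 of 216 controls (25%) and 35 of 216 experimental patients (16%) are restrained. As nobody is matched, b and c depend on an arbitrary pairing:

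| Pairing imposed | b | c | Statistic | p |
|---|---|---|---|---|
| No pair with both restrained | 54 | 35 | 19²/89 = 4.06 | 0.044 |
| 35 pairs with both restrained | 19 | 0 | 19²/19 = 19.0 | 0.00001 |

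The two-sample test of proportions needs no pairing. The pooled proportion is 89/432 = 0.206, z = 2.26, p = 0.024. The McNemar p-value reflects the invented pairing, so it is undefined for these data.

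**3. McNemar's test within the experimental group, no intervention effect.** Both groups are given the same change over time. For pain falling from 70% at admission to 60% at discharge, with latent correlation 0.3, the discordant probabilities are 0.238 and 0.138. With n = 194 the expected counts are 46.3 and 26.9, and (46.3−26.9)²/73.1 = 5.1, above the critical 3.84. By simulation (20,000 runs):

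| Change over time, same in both groups | McNemar rejects, uncorrected | McNemar rejects, continuity-corrected or exact | Two-sample test at discharge rejects |
|---|---|---|---|
| 70% to 60% | 63% | 58–59% | 5% |
| 70% to 50% | over 99% | 99% | 5% |
| 50% to 45% | 19–20% | 16% | 5% |

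For 70% to 60%, the uncorrected rate runs from 54% at correlation 0 to 75% at correlation 0.6.

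With restraint-type rates, visits assumed independent and n = 216 (uncorrected test), McNemar's test rejects in 23% of runs for 25% to 20%, 74% for 25% to 15%, and 99% for a rise from 10% to 25%. The two-sample test again stays at about 5%.

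**4. Which outcomes are affected.** Restraints and psychotropic use are naturally yes/no. Falls and readmissions are affected only if reduced to yes/no. Readmission also has no meaningful admission value with which to form a within-patient pair.

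**The case against.** The best defence is that McNemar's test has proper uses in this study. Each patient is seen up to four times (Table 2), and the same section promises longitudinal change. Staff answer a knowledge questionnaire before and after the intervention, and nurses' knowledge is a main outcome. Both are within-person comparisons if the staff answers are linked. This stands: a reader might infer that the test has no place here, and that would be wrong. But the article does not confine it to these uses, and neither estimates the between-group effect on patients.

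Four other stronger readings are not supported:

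- **Length of stay.** It is continuous, so the article assigns it to the t-test or ANCOVA, not to McNemar's test.
- **Falls and readmissions.** The article speaks of numbers of falls and of readmissions. These may be counts, so it does not clearly assign them to McNemar's test.
- **A one-group design.** The abstract's "repeated observations, taken at baseline, post-intervention, and at one and three months post-intervention" might be taken for a single cohort measured before and after. It is a loose summary of the visit schedule and never says one group. The pre/post wording in the analysis section can equally mean the pre-implementation cohort against the post-implementation cohort. Both are ambiguous rather than contradictory.
- **No case-mix adjustment at all.** ANCOVA is named in the same sentence, and the grammar leaves open whether the two tests replace it or accompany it. The exact covariates are a detail that an article may leave to an analysis plan.

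It is also fair to say that the simulated rates rest on assumed inputs, and that a control group exists to warn against misreading a within-group change.

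**Conclusion.** The point holds as a stated method that does not fit the design. It is not a detail left to a later document, because the article names the test and ties it to the intervention effect. It should be corrected before analysis, since restraints and psychotropic use are main outcomes.

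That McNemar's test cannot address the contrast between unmatched groups follows from the design and needs no assumption. The size of the misreading does need assumptions: about 60% false attribution for a 10-point fall in pain from 70%, about 16–20% for a 5-point fall from 50%, and near certainty for a 20-point fall from 70%, all with n = 194, latent correlation 0.3 and no intervention effect. These figures apply only if the within-group test is reported as the effect of the programme.

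**What to change.** In the Statistical analysis section:

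- State that the patient-level contrast is experimental versus control group, and that the pre/post wording means the cohort recruited before implementation against the cohort recruited after it.
- Analyse binary outcomes with an independent-groups method. One suitable choice is logistic regression (GEE or a mixed model for repeated visits) with group, hospital, the admission value where one exists, and admission covariates already collected, such as SPMSQ, Charlson and Barthel. Report the adjusted effect with its 95% confidence interval.
- If falls or readmissions are kept as counts, use a count model.
- Keep McNemar's test only for stated within-person comparisons: linked before/after staff questionnaire items, or descriptive change within a group.

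The cost is a few sentences. No new data are needed, and the stated 432 does not rest on the test being replaced. According to Study progress, the control group was still recruiting and the intervention was still being worked on, so the change could be made before any between-group patient data existed.

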**PwD and IC**					
Inclusion and exclusion criteria	–	✓			
Cognitive Assessment (SPMSQ)	10	✓	✓		
Clinical data and history	–	✓			
Medication record	–	✓	✓	✓	✓
PAINAD	5	✓	✓	✓	✓
Morbidity (falls, pressure ulcers, restraints, etc.)	–	✓	✓	✓	✓
Nutritional assessment (MNA)	6 + 12	✓		✓	
Charlson Comorbidity index	19	✓			
Barthel	10	✓	✓	✓	✓
ADL (Katz)	6	✓	✓	✓	✓
NPI-Q	12	✓	✓	✓	
Satisfaction (PSS)	11		✓		
Costs (RUD)	–	✓		✓	
Caregiver Reaction (CRA)	24			✓	
Caregiver experience (IEXPAC)	16	✓	✓	✓	✓
Follow –up (use of health and social services)	–			✓	✓

Measurements performed in PwD include use of mechanical restraints, pain management, number of falls, comorbidity (Charlson Index) [28, 29], nutritional assessment (MNA) [30, 31], pressure ulcers, psychotropic medication administration, functional capacity (Barthel) [32, 33], length of stay and readmissions, behavior (NPI) [34, 35], activities of daily living (Katz) [36, 37], and pain assessment for PwD (PAINAD) [38, 39].

Continuity of care: Nursing discharge planning and information given to patients and families.

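### About eleven co-equal main outcomes share one p<0.05 threshold with no primary outcome or visit, so the risk of a false positive is substantial

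*Protocol article*

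**What the plan says.** The Statistical analysis section of the protocol article fixes four things.

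- **The main outcomes.** The list begins "Main outcome measures include quality of care and comorbidity (physical restraints, psychotropic medication, falls, functional capacity, pain assessment, length of hospital stay" and closes that group with readmissions. It then adds "continuity of care (informal caregiver reaction, multidisciplinary and intersectoral communication) economic costs of hospital and community care and nurses’ level of knowledge". All carry the same label, and none is ranked above another.
- **The visits.** "Outcomes measured will assess longitudinal changes from all the collection phases; baseline (admission), discharge, 1 month and 3-month follow-up". No visit is singled out.
- **The threshold.** One level serves every test: p below "0.05 will be considered significant".
- **The sample size.** The 432 participants come from "assuming an improvement in patients with pain around 50" per cent, a precision of 5%, 95% confidence and 10% dropout. Neither a pain instrument nor a visit is attached to that assumption.

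Table 2 schedules PAINAD at admission, discharge, 1 month and 3 months. Study progress reports 173 control patients recruited and the intervention still in preparation at the hospitals.

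**The concern.** The aim is to assess whether the programme is effective, and the final report is meant to ease its introduction in other hospitals. With about eleven outcomes of equal rank and one unadjusted threshold, the protocol does not say which result will decide that question. Two consequences follow. The chance that something reaches p<0.05 when nothing has changed is well above 5%. And the investigators could decide after seeing the data which outcome, at which visit, to put forward. Pain drives the sample size but has no special standing in the analysis, so the one outcome that might serve as an anchor does not.

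**Working it through.** **Sample size, reproduced first.** Inputs from the Statistical analysis section: proportion 0.50, precision 0.05, 95% confidence, 10% dropout.

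- n = 1.96² × 0.5 × 0.5 / 0.05² = 384.1, so 385.
- With dropout: 385 / 0.90 = 427.8, so 428.
- Rounded up to a multiple of 8 (four hospitals, two groups): 432. This matches Table 1, where 54 × 4 × 2 = 432.

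The stated figure therefore reproduces as the precision of one proportion in one group. No between-group difference and no power enter it.

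**Count of main outcomes.** Seven under quality of care and comorbidity: restraints, psychotropics, falls, functional capacity, pain, length of stay, readmissions. Four more: caregiver reaction, communication, costs, nurses' knowledge. The total is 11 on the smallest count. It is 13 if the two kinds of communication, and hospital and community costs, are counted separately.

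**Chance of at least one p<0.05 if the programme has no effect.** For k independent two-sided tests (sidedness is not stated, so two-sided is assumed) the chance is 1 − 0.95^k.

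| Tests | Chance |
|---|---|
| 1 | 5.0% |
| 7 | 30.2% |
| 11 | 43.1% |
| 13 | 48.7% |

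*Correlated outcomes.* The documents give no correlations, so a common value was assumed and simulated with 200,000 replicates for 11 tests: 37% at 0.3, 30% at 0.5, 22% at 0.7.

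*Favourable direction only.* 1 − 0.975^11 = 24.3% under independence. Correlation lowers this too: 19% at 0.3 and 11% at 0.7.

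**If visits are tested separately.** The count follows Table 2, with assumptions where it is silent:

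- restraints, psychotropics, falls, functional capacity and pain at three post-admission visits: 15;
- readmissions at two: 2;
- length of stay, caregiver reaction, communication, costs and knowledge once each: 5.

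The total is 22, and 1 − 0.95^22 = 67.6% under independence. With assumed correlations of 0 to 0.3 between outcomes and 0.3 to 0.7 within an outcome over visits, the simulated range is 52% to 66%. Counting favourable results only, it is 27% to 41%, or 43% if all 22 tests are independent.

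**With one primary outcome.** A single prespecified test at two-sided 5% has a type I error of 5%. Bonferroni over the 11 outcomes (0.05/11 = 0.0045 each) would give 4.9%.

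**What 432 would give for pain.** After 10% dropout, 216 × 0.90 = 194 per group. With a control rate of 50% and illustrative experimental rates that are not in the documents, power at two-sided 5% is 85% for 35%, 51% for 40% and 16% for 45%.

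**The case against.** The strongest reply is that multiplicity adjustment and the labelling of secondary outcomes often sit in an analysis plan, which is not shown here. That is fair as far as the adjustment method goes, and its absence is not held against the article. But the choice of primary outcome belongs in the protocol, and the article makes a choice: it gives about eleven outcomes the same rank.

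Several stronger readings are tempting and do not hold.

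- **Any one significant result proves the programme works.** The protocol states no such rule. It sets a threshold for significance and separate objectives for quality of care, continuity, costs and knowledge. The difficulty is that it gives no other criterion.
- **Every main outcome is tested at several visits.** Table 2 schedules the caregiver reaction scale at 1 month only, length of stay is one value per patient, and staff knowledge is a before-and-after measure. Nor does the text say that each visit gets its own test; one longitudinal analysis per outcome would be compatible with it.
- **Functional capacity has two competing scales.** The list of measurements ties functional capacity to Barthel and names Katz separately, for activities of daily living.
- **A false claim of effectiveness is likely.** Over 11 independent tests a false result in the favourable direction has a chance of about 24%. Even with 22 tests it stays below one half.

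**Conclusion.** The concern stands in a limited form. The protocol article ranks about eleven main outcomes equally, applies one p<0.05 threshold, and names no primary outcome or time point, while sizing the study on pain alone. Under no effect, the chance of at least one p<0.05 over 11 tests is 43% if they are independent and about 22% to 37% under assumed correlations of 0.7 to 0.3. It is higher if visits are tested separately. The risk is substantial; the documents do not support calling it likely that the programme will be falsely declared effective. The correlations and the 22-test count are assumptions, but across the range examined the chance of some false positive stays at more than four times the nominal 5%.

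A reader might also infer that making pain primary yields an adequately powered comparison. It does not follow: 432 is a precision figure for a single proportion.

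**What to change.** Before experimental-group data exist, amend the Statistical analysis section as follows.

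1. Name one primary outcome, with its definition and visit. The natural candidate is the proportion of patients with pain on PAINAD at discharge, experimental versus control, tested at two-sided 5%. Pain is the outcome behind the sample size, and discharge closes the hospital stay in which the programme is delivered. The 1-month visit is also in person, so the investigators may have reasons to prefer it. They must also state the PAINAD cut-off that counts as pain, since the article gives none.
2. Make all other outcomes secondary: either Holm-adjusted, or labelled exploratory and reported with 95% confidence intervals.
3. State that 432 comes from a single-proportion precision calculation (50% ± 5%, 10% dropout) and is not a power calculation for the between-group comparison.

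The cost is protocol wording. PAINAD is already collected at every visit, so data collection does not change. The downside is that p-values for the other outcomes lose confirmatory status. With only control recruitment reported so far, the choice can still precede any comparative data.

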When a PwD is admitted to a fast-paced, noisy acute hospital, the unknown environment can trigger disorientation and agitation, where distress is also experienced due to disruption of normal routine [10]. This can be challenging for nurses that are expert in the unit specialty, in this case traumatology, but are not specifically trained to look after PwD. Lack of training focused on care of PwD or cognitive impairment can cause professionals to feel incompetent and frustrated and lead to high levels of stress. This can result in heightened clinical practice risk [11, 12]. Additionally, the unpredictable nature of dementia means that PwD can show lucidity one day, or inability to follow instructions the next day, which can worsen the situation [13]. As such, educational interventions should focus on how staff identifies PwD experiences and shares knowledge on how to manage challenging behaviors through development of person-centered practices and focusing on priorities [14].

A study in the United Kingdom showed that 57% of hospitalized PwD presented aggressiveness, 42% had sleeping problems and 35% suffered from anxiety [15]. To prevent delirium and aggressiveness in PwD, we can act on triggers, modify the environment, foster psychosocial abilities or optimize resources. Furthermore, physical restraints are used to control agitation/aggressiveness when there is potential danger to the patient and his/her environment and he/she cannot be controlled with other measures (verbal or pharmacological). Restraints can only be used when other measures fail [16]. However, in Spain, 25% of hospitalized patients with moderate to severe dementia presenting agitation are physically restrained; one of the highest rates in countries in Europe [17].

Similarly, psychotropic medication administration is also higher in Spain than in any other European country, identified in 54% of PwD [18]. Studies found an association between use of multiple psychotropic medications and a higher risk of fall injuries, hospitalizations and death. Non-pharmacological alternatives are safer and can impact positively in social economic burden and patient comfort [19].

Another important aspect to consider in care of hospitalized PwD is pain management. This can also be very challenging for nurses, especially when it comes to initiating pain assessment and adequate use of tools. Moreover, cognitive impairment limits the ability to communicate and describe pain [20].

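### The stated analysis of psychotropic medication, a main outcome, nets starters against stoppers; compare use at discharge between groups with adjustment for use at admission

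*Protocol article*

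**What the plan says.** The Statistical analysis section of the protocol article gives the main outcomes as a list: "Main outcome measures include quality of care and comorbidity (physical restraints, psychotropic medication, falls, functional capacity, pain assessment", followed by length of stay, readmissions and others. The abstract's Methods paragraph puts it this way: "Quality of care and comorbidity will be analyzed based on the use of restraints and psychotropic medication". The Measurements section lists "psychotropic medication administration". None of these places separates drugs the patient already took from drugs started on the ward, and none states the unit of the outcome.

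Table 2 has a row "Medication record" ticked at admission, discharge, 1 month and 3 months. On analysis, the article says: "Outcomes measured will assess longitudinal changes from all the collection phases; baseline (admission), discharge, 1 month and 3-month follow-up". It names ANCOVA for the intervention effect without naming a covariate, Student's t-test for continuous variables and McNemar's test for categorical variables.

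The Background states that "psychotropic medication administration is also higher in Spain than in any other European country, identified in 54% of PwD". That describes people with dementia in general. It is not given as use on arrival at a traumatology unit.

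**The concern.** The control and experimental groups are different patients, recruited in consecutive periods without randomisation. The effect of the programme on a yes/no outcome is therefore a difference between two independent groups. McNemar's test compares, within one group, those who move from no use to use with those who move from use to no use. It yields one net shift per group and no between-group estimate. A between-group comparison of change is better, but it still adds starters and stoppers with opposite signs and carries the variance of both.

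This matters because the programme reaches patients only after arrival. Some of the use counted at discharge will have begun before admission, and drugs started on the ward are only part of what moves the outcome. If many patients arrive on a psychotropic, stopping and continuing among them adds noise to any effect on new starts. A difference in admission use between the two periods can also distort the comparison unless patients are compared within levels of admission use.

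**Working it through.** **The plan's own figure.** The article's sample size concerns pain. Precision of one proportion: n = 1.96² × 0.5 × 0.5 / 0.05² = 384.1, so 385; allowing for 10% dropout, 385 / 0.9 = 428. This is close to the stated 432, which equals 8 cells of 54. Hence 216 per group, and 216 × 0.9 = 194 evaluable. No power is stated for psychotropic use.

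**Inputs for the illustration**
- Users at admission: 54%. This borrows the Background figure; reading it as arrival prevalence is an assumption.
- Still users at discharge: 90%, the same in both groups (assumed; range 85% to 95%).
- Ward starts among admission non-users: 30% control, 15% experimental (assumed).
- 194 per group, two-sided 5%, normal approximation: power = Φ(d/SE − 1.96).

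**Use at discharge**
- Control: 0.54 × 0.90 + 0.46 × 0.30 = 0.624.
- Experimental: 0.54 × 0.90 + 0.46 × 0.15 = 0.555.
- Difference d = 0.069.

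**The netting.** Starters are 0.46 × 0.30 = 13.8% in controls and 0.46 × 0.15 = 6.9% in the experimental group. Stoppers are 0.54 × 0.10 = 5.4% in both. Of 194 controls, about 27 start and 10 stop, a net change of 8.4 points. Of 194 experimental patients, about 13 start and 10 stop, a net change of 1.5 points. McNemar's test works on each pair of counts separately.

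**Comparing change between groups.** The variance per patient is starts + stops − net².
- Control: 0.138 + 0.054 − 0.084² = 0.1849.
- Experimental: 0.069 + 0.054 − 0.015² = 0.1228.
- SE = √[(0.1849 + 0.1228)/194] = 0.0398. Power = Φ(0.069/0.0398 − 1.96) = 41%.

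**Adjusting for (stratifying by) admission use.**
- SE = √{[0.54 × 2 × 0.90 × 0.10 + 0.46 × (0.30 × 0.70 + 0.15 × 0.85)]/194} = √(0.2525/194) = 0.0361.
- Power = Φ(0.069/0.0361 − 1.96) = 48%.

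**New starts among admission non-users.** 0.46 × 194 = 89 per group. SE = √[(0.21 + 0.1275)/89] = 0.0616. Power = Φ(0.15/0.0616 − 1.96) = 68%.

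**Range.** The same formulas give:

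| Admission use | Continuing | Starts | Change | Adjusted | New starts |
|---|---|---|---|---|---|
| 54% | 85% | 30% vs 15% | 36% | 43% | 68% |
| 54% | 90% | 30% vs 15% | 41% | 48% | 68% |
| 54% | 95% | 30% vs 15% | 49% | 56% | 68% |
| 54% | 90% | 30% vs 20% | 20% | 24% | 34% |
| 54% | 90% | 40% vs 20% | 56% | 68% | 85% |
| 25% | 90% | 30% vs 15% | 77% | 82% | 88% |

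**Imbalance at admission.** With 54% users, the 95% range for a chance difference in admission use is ±1.96 × √(2 × 0.54 × 0.46/194) = ±9.9 points, larger than the 6.9-point effect. At control rates, admission users change by −0.10 on average and non-users by +0.30. A 9.9-point imbalance therefore moves the difference in change by 0.099 × 0.40 = 4.0 points. Comparing within levels of admission use removes this shift.

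**The case against.** The strongest reply is that the baseline is already in the plan. Medication is recorded at admission, change from admission is to be assessed, and ANCOVA is named. If ANCOVA was meant to take admission use as its covariate, it reaches practically the same 48% and the proposal adds nothing to power. This stands as far as it goes, but the article names no covariate, and the test it assigns to categorical variables is McNemar's.

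A second reply is that a condensed article may leave the coding of one outcome among many to the full protocol or analysis plan. That is fair, so missing detail on coding is not the complaint. The point rests on the analysis that is stated.

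A reader might infer that the outcome counts any use, that more than half of patients arrive on a psychotropic, and that the plan is therefore left with 28% power. The documents do not support this. No section says any use. The 54% is not tied to arrival or to hip-fracture inpatients. The 28% belongs to an unadjusted comparison at discharge (SE = √[(0.624 × 0.376 + 0.555 × 0.445)/194] = 0.0498; Φ(0.069/0.0498 − 1.96) = 28%), which the article does not describe.

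Finally, the staff training covers psychotropic medication without restriction to new starts, so existing drugs may be affected too. If continuation also fell from 90% to 80% in the experimental group (again an assumption), use there would be 0.54 × 0.80 + 0.069 = 0.501, a crude difference of 12.3 points with about 69% power. Overall use is thus a legitimate target, and new starts should not replace it.

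**Conclusion.** The point holds in a limited form. For this yes/no main outcome, the analysis stated for categorical variables offsets starters against stoppers and does not give a between-group comparison adjusted for admission use. Against the fairest reading of the plan, a between-group comparison of change, adjustment raises power from about 41% to about 48% in the main illustration, and by 4 to 12 points across the scenarios shown. It also protects the comparison from a difference in admission use between two non-randomised periods, though not from other differences between the periods.

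The size rests on assumed start and continuation rates and on borrowing the 54% as arrival prevalence. The direction is the same in every scenario tried, including 25% use at admission. The power gain is nil if admission use was already the intended ANCOVA covariate; in that case only the wording needs correcting. No power was planned for this outcome, so these figures compare analyses with one another, not with a stated target.

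**What to change.** State the outcome as psychotropic use at discharge, taken from the medication record, and compare it between the control and experimental groups with adjustment for, or stratification by, use at admission. Logistic regression with admission use as a covariate, or a Mantel-Haenszel comparison, would serve. Report two supporting components: new starts among patients not on a psychotropic at admission, and continuation among those who were. The 1-month and 3-month records can be handled in the same way.

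The cost is outcome wording and one covariate, with no new data. The Study progress section reports 173 controls recruited and the intervention still in preparation, so the definition could be fixed before any experimental-group results exist. The downside is small: the new-start component uses fewer than half of the patients under the 54% assumption and says nothing about withdrawal of earlier drugs. That is why the adjusted analysis of all patients should lead and the components should only support it.
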